## Abstract

**Background:**

Suffering from cancer confronts both the patient and their partner with a number of psychosocial challenges in various aspects of their life. These challenges may differentially impact on quality of life, coping ability and compliance to treatment. This especially holds true for haemato-oncological diseases. To date, psychological interventions have predominantly been developed for oncological patients however specific interventions for partners of haemato-oncological patients are rare. In this study we aim to conduct a psycho-oncological group-intervention for partners of patients with haemato-oncological diseases. The aim of the intervention is to significantly reduce symptoms of depression and anxiety in the partners and the patient, as well as enhancing dyadic coping.

**Methods:**

The design of the INPART-study is an unblinded, randomised controlled trial with 2 treatment conditions (experimental and control) and assessments at baseline, 3 and 6 months. It will be conducted at three study centres: the university medical centre’s in Leipzig, Hannover and Ulm. The outcome criteria will be a reduction in depressive and anxiety symptoms as well as an improvement of dyadic coping.

**Discussion:**

This trial shall provide information regarding the efficiency of a psycho-oncological intervention for partners of patients with haemato-oncological diseases and give references to the possible outcome in terms of dyadic coping and the reduction of mental strain.

The study was supported by a grant from the German José Carreras Leukaemia Foundation.

**Trial registration:**

ISRCTN16085028; 20/03/2019.

## Background

Cancer does not only confront the patient with psychosocial challenges but also their partner [1, 2]. Pitceathly and Maguire [3] found that 20–30% of partners of cancer patients suffer from psychological stress rising to 50% when the cancer is highly progressive. This is particularly true to partners of haemato-oncological patients. Compared to other cancer types, the percentage of partners and caregivers of patients with haemato-oncological cancer affected with depression and anxiety is considerably higher [4]. Adjustment and anxiety disorders, depression, as well as sleeping disorders are among the most frequently reported distress-related symptoms. In addition to their concern about the patient, the uncertainty and the anxiety that arises from the diagnosis, they have to cope with changes which affect almost every aspect of their daily lives: their social role, financial situation, limitation of recreational activities and communication problems within their relationship [5]. Studies show that the psychological load for partners is comparable to that of the patients [6] and in some cases even higher [7, 8]. Simultaneously, the social environment does not perceive these problems adequately since the specific burden often remains invisible. This might be due to the fact that the main focus is on the patient. Partners tend to report their distress only rarely. As a result partners receive less social, health-care related and psychological support than the patient [9, 10] with negative consequences for both the patients and their partners as well as for dyadic coping (DC).

For haemato-oncological diseases the mentioned psychosocial burdens are particularly pronounced. Patients, as well as their partners, have to deal with significant limitations regarding their functionality and quality of life. The new situation requires high levels of adaptation by both the patient and their partner [11]. Haemato-oncological diseases are characterised by treatment interventions of long duration, that can cause severe therapy associated risks, the consequences of which can affect the patients and their partners years after treatment, for example in the case of stem cell transplantation [12, 13]. During treatment, the course of disease is highly unpredictable; people have to cope with the uncertainty of the success of the treatment as well as the possibility of a sudden life-threatening crisis. It is easily understandable that this can lead to severe emotional distress. Partners are often torn between caring for the patient and their other life commitments such as employment, child care and managing the household. Additionally, immunocompromised patients are required to make lifestyle changes such as restricting their social contact which can impact significantly on the mood of the person concerned. It is clearly evident that all of these difficulties influence the quality of the relationship between patient and partner, often resulting in profound communication difficulties. So far no data concerning haemato-oncological patients are available, however Manne et al. [14] showed in a group of breast cancer patients that the support of the partner is extremely important for the coping ability of the patient. This indicates strong support for the partner positively helps the patient coping ability. Conversely, a lack of support for partners can lead to maladaptive coping of the patient given that high scores of psychological stress in the partner have shown to have a negative consequence on quality of life and distress to the patient [15]. Considering the psychological stressors, described above, it is very likely that this is true, or even more pronounced, in haemato-oncological diseases.

Various psycho-oncological interventions aiming at reducing psychological load or an improvement in symptom management have been developed and successfully evaluated. Most of them focus on patients or the couple as a dyad [16, 17]. For partners there has been far less research [18] despite available evidence suggesting a better outcome for solely partner focused interventions than family based treatment - even for the patient [19]. There is no correlation between the patient’s course of disease and the perceived stress of the partner indicating an asynchronous process. Given that the needs and burdens of patients and partners differ over time, future interventions need to address the specific problems adequately both with regard to content and methods. With our INPART program we want to take a big step to closing this gap. In comparison to the established interventions INPART is addressing the partners solely by giving them the possibility to talk openly about the specific burdens in the safety of a homogenous group constellation. Established programs aim to reduce the psychological load of the patient or the partner, but fail to look at the interactions within the dyad. With the randomized controlled trial (RCT), described in the following, we want to investigate this reciprocal influence anticipating that by helping the partners to cope will have a positive influence on the dyadic coping and thus also on the psychological well-being of the patient.

### Aims of INPART

The aim of the present study is to examine the effectiveness of the INPART (INtervention for PARTners) program in reducing psychological distress (measured via depression and anxiety) and improving DC in partners and patients with haemato-oncological cancer in comparison to care as usual (CAU). The planned proceeding shall contribute to a better specificity of treatment and thereby to sustainable effects and significant benefits within the patient-partner-dyad.

### Intervention

The INPART program was created specifically for this study. It is a mixed intervention consisting of psychoeducational, cognitive-behavioural and imaginative elements. The decision, on which contents were to be included in the program, were based on research on the supportive care needs questionnaire for informal caregivers of cancer patients and cancer survivors [20]. The structure of the session is the same for each week, as can be seen in Table 1. At the end of the group phase each participant will get the chance for one or two individual psychotherapy sessions in order to face specific problems. Planned topics are: the individual handling of depression and anxiety, stress management, conflict training and managing difficult situations within the dyad (sexuality, communication problems).

**Table 1 Tab1:** Overview of the standardized structure of the sessions

Treatment components	Content
Short opening discussion about today’s feeling	How do I feel at the moment? Questions about last session, if necessary
Monitoring home practice	Group conversation about the assigned exercises
Basic information	Psycho-education about today’s topic (for example communication within relationships)
Discussion of session topic	Talk between the participants led by the therapist: What do I experience as helpful? How do I cope with severe problems? Motivation: Partners shall learn from the model of others, how to cope more functionally and to be helpful for others
Practical exercise (incl. Home assignment)	Exercises for in-depth practice of the session topic, e.g., communication role play, integration of positive activities into daily routine
Outline for the next session	Short outlook on the topic of the next session
Relaxation/imagination/mindfulness	Introduction to established supportive interventions such as progressive muscle relaxation. Aims: Improvement of relaxation skills, resource activation and mindfulness practice to better cope with negative experiences, thoughts and feelings
Evaluation	Participant evaluates each session at the end

The program comprises of 5 weekly sessions lasting 1.5 h and additional home practice assignments. Groups consist of 6 to 8 participants. A presentation via Microsoft Powerpoint supports the structure of the course. In each session the participants receive material supporting the actual topic, a folder containing further information and home practice instructions for the forthcoming week. Table 2 shows the content of the INPART program per session.

**Table 2 Tab2:** Structure and content of the INPART sessions and home practice

Session	Content	Form of relaxation techniques
1	● Introduction to the course and goals of INPART	Progressive muscle relaxation (PMR)
	● Information about the specific burdens of partners of patients with cancer	
	● Identification and activation of resources	
2	● Identification of negative appraisals, interpretations and meanings ● Recognizing and down-scaling of excessive self-expectations to facilitate daily life	Guided imagery: encouragement of a benevolent companion
3	● Communication within relationship: Introduction to basic rules of successful communication, non-verbal communication, gender differences in communication	Autogenic training
4	● Dealing with emotions, (focus on anxiety)	Mindfulness-based stress reduction
	● Promotion of functional anxiety management	
	*Aim*: Reduction of dysfunctional coping and regain of control	
5	*Final session*: ● Coping in daily life	Guided Imagery: safe place
	● Outlook: taking next steps	
	● Reflection of the program	

In order to test the standard operating procedures and evaluate the feasibility of the INPART program a pilot study was carried out. Between October and December 2017 patients and their partners were recruited as outlined for the INPART RCT. The participants were not screened for distress in order to be considered eligible for the study. All participants were assigned to the intervention condition as there was no control group. In January/February 2018 two trials were carried out in Ulm and Leipzig (*N* = 6). The pilot phase included a pre- and post- questionnaire and an evaluation of each INPART-session to find out which topics are relevant and to improve the final version of the intervention. Planned improvements were: less theory and more practical exercises, greater focus on self-care, a substantial reduction of the homework (experienced more as a burden by the participants) and the establishment of an additional session with a special topic (i.e. cancer and children). The pilot phase showed that the program was feasible and well received by the participants.

### Main study hypotheses

To alleviate depression as well as anxiety and to promote psychological well-being in partners of individuals with haemato-oncological disease the INPART-intervention was developed and will be tested in the proposed RCT. Principal hypothesis: A manualized group psychotherapy to treat clinically significant depressive and anxiety symptoms in partners of cancer patients with haemato-oncological disease will result in a greater reduction of depression and anxiety symptoms than in a control treatment of usual intervention (expected effect size ≥0,30) at three (t1) and six months (t2) after commencing intervention. In addition, the INPART program will lead to significant better DC. Secondary hypotheses: The INPART-intervention will result in better quality of life, better quality of the relationship and more self-efficacy than the control intervention. Between t1 and t2 a structured short-time psychotherapy in the intervention group will lead to further positive effects in the dependent variables compared to that of the treatment as usual group.

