## Methods / design

### Study design

The design of the INPART-study will be an unblinded, randomized controlled trial with 2 treatment conditions (experimental and control) and assessments at baseline, 3 and 6 months. It will be conducted at three study centers: the university medical centre in Leipzig, Hannover and Ulm. Following an initial screening procedure, eligible partners (necessary requirement PHQ-9 or GAD-7 > 9) will be randomized into one of two groups at which baseline-assessment will take place (see Fig. 1). Participants will be either assigned to the intervention group (IG) or to the control group (CG). T1 is 3 months after the start of the intervention. Directly after the intervention, before t1, subjects of the intervention group will have the possibility of one additional single session in order to talk about individual topics/problems (i.e. hope, death and loss). Subjects of the control group will be treated as usual (optional unspecific contacts with a psycho-oncologist). At all assessments partners and patients are asked to fill out the questionnaires. The study protocol has been approved by the ethical review boards of each of the three centres. The registered project number is DJCLS R 12/36.

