#### Statistical analyses

In order to quantify the collected data descriptively summary statistics like mean values, variances, measures for value distribution and frequencies will be calculated for characteristics like frequencies of cancer types, gender, age and quality of relationship. For exploratory data analysis cross table evaluations will be performed including sociodemographic and disease specific control variables in order to find possible age or educational related effects. Correlation analyses will be used to assess the strength of associations between variables. At the interferential level mean comparisons via t-test or Mann-Whitney-U-Test will be employed to assess the efficacy of INPART in comparison to the control group at three different time intervals. We expect that that the level of depression and anxiety will change over time and a reduction is highest in the treatment group. Main analyses will be performed using a multivariate analysis of variance with repeated measures (MANOVA). In addition, multiple regression analysis will be applied to identify predicting factors (Table 4).

**Table 4 Tab4:** Descriptive and inferential statistics

Descriptive statistics	˗ Exploratory data analysis (value distribution, analyses of variance)
	˗ Cross table evaluation incl. Control variables (sociodemographic, disease specific)
	˗ Correlation analysis
Inferential statistics	˗ Comparisons of means (t-test or Mann-Whitney-U-test)
	˗ Multivariate analyses of variance (for multiple dependent variables), general linear model
	˗ (Multiple) logistic Regression for identification of predictors and determination of effectiveness
	˗ Actor-partner-interdependence model in order to investigate reciprocal influence within the dyad

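### The t1–t2 hypothesis credits a short psychotherapy that two arms randomised once can test only as part of the INPART package, and the individual sessions and control contact are described inconsistently

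*Protocol article*

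**What the plan says.** **Hypotheses.** In Main study hypotheses, the principal hypothesis credits "A manualized group psychotherapy to treat clinically significant depressive and anxiety symptoms" with a greater reduction of symptoms "at three (t1) and six months (t2) after commencing intervention". A secondary hypothesis in the same section then states: "Between t1 and t2 a structured short-time psychotherapy in the intervention group will lead to further positive effects". That sentence goes on to name the usual-care group as the comparator.

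**Design.** Study design describes a "randomized controlled trial with 2 treatment conditions (experimental and control) and assessments at baseline, 3 and 6 months". Participants and procedure has partners assigned at random to one of the two groups. No second randomisation is described. Statistical analyses plans mean comparisons to "assess the efficacy of INPART in comparison to the control group at three different time intervals".

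**Individual sessions.** The Intervention section says: "At the end of the group phase each participant will get the chance for one or two individual psychotherapy sessions". Study design says: "Directly after the intervention, before t1, subjects of the intervention group will have the possibility of one additional single session".

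**Control.** Study design has the control group "treated as usual (optional unspecific contacts with a psycho-oncologist". The Control group section gives every control partner one structured consultation of about 30 minutes and a booklet, and also labels this care as usual. The Randomization procedure section says that other psycho-oncological interventions are recorded and taken into account in the analysis.

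**The concern.** The secondary hypothesis names one component, places it after t1 and says that it will produce further gains. A reader of the results would take a widening gap between t1 and t2 as evidence for that component. In the intervention arm, everyone offered the individual sessions has also been assigned the five-session group programme, so a widening gap could equally be a late effect of the group, and a stable gap could hide a useful therapy that offsets a fading group effect. The t2 difference is also claimed for the group therapy in the principal hypothesis, so the same result has two stated causes.

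The text adds a timing problem: the therapy that the hypothesis places between t1 and t2 does not appear in the sections that describe treatment. The control condition is the reference for every between-arm result, and it too should have one description.

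**Working it through.** **1. The plan's own figure.** N = 162 is not in dispute. With f = 0.25, alpha 0.05, power 0.80 and noncentrality f² × N, an ANOVA with 2 groups × 3 centres = 6 cells and 2 numerator degrees of freedom needs 158, which rounds up to 162 as a multiple of 6. The article does not say which setting was used. Nothing below depends on it.

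**2. The individual sessions, side by side.**

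| Section | Number | Timing |
|---|---|---|
| Main study hypotheses | not given | between t1 and t2 |
| Intervention | one or two, offered | end of the group phase |
| Study design | one, offered | after the intervention, before t1 |

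The programme has 5 weekly sessions, so the group phase ends in about week 5. Study design puts t1 at 3 months after the start, about week 13. The end of the group phase is therefore about 13 − 5 = 8 weeks before t1. Intervention and Study design agree on timing and differ in number; both conflict with the hypothesis on timing.

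**3. What the t1–t2 contrast can show.** Let g1 and g2 be the effect of the group programme versus control at t1 and t2, and s1 and s2 the additional effect of the individual therapy. The between-arm differences are d1 = g1 + s1 and d2 = g2 + s2, so

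d2 − d1 = (g2 − g1) + (s2 − s1).

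This is one observed quantity with more than one unknown, at any sample size.

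*Therapy after t1, as the hypothesis states.* Then s1 = 0 and s2 = d2 − k × d1, where k = g2/g1 is the unknown share of the group effect that persists. The principal hypothesis expects an effect of at least 0.30, with no metric given. Using 0.30 for d1 in those same units (the d2 and k values are illustrations, not protocol figures):

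- d2 = 0.30: k = 1, 0.5, 0 gives s2 = 0.00, 0.15, 0.30.
- d2 = 0.45: k = 1.5, 1, 0.5, 0 gives s2 = 0.00, 0.15, 0.30, 0.45.
- d2 = 0.20: k = 2/3, 0.5, 0 gives s2 = 0.00, 0.05, 0.20.

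*Therapy before t1, as the treatment sections state.* Then s1 is already inside d1. If the therapy works and its effect holds (s2 = s1), it cancels and the contrast is g2 − g1 alone.

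**4. What a separate claim would need.** One route is to re-randomise the intervention arm at t1: 162/2 = 81, split 40/41, with no losses. The detectable difference at 80% power, two-sided 5%, is (1.960 + 0.842) × √(1/40 + 1/41) = 2.802 × 0.222 = 0.62 SD. Adjusting for the t1 score multiplies this by √(1 − r²): 0.54 SD at r = 0.5 and 0.44 SD at r = 0.7. Both correlations are assumed. If 0.30 is read as SD units, also an assumption, unadjusted power is Φ(0.30/0.222 − 1.96) = Φ(−0.61) = 27%.

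**5. Control contact.** Under the Control group section it is about 0.5 hours for everyone, plus the booklet. Under Study design it is optional, so it could be zero.

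**The case against.** The secondary hypothesis names usual care as its comparator. It can be read as saying only that the arm which also receives individual therapy will pull further ahead of usual care, and two randomised arms can test that. This stands: the sentence never promises to separate the therapy from the group programme. What remains is that its grammar makes the therapy the cause, and the proposed rewording simply states the package reading.

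A reader might infer that no therapy after t1 is planned. The documents do not go that far. The study-procedure figure is not shown and the article condenses a fuller protocol. What can be said is that the text places the described sessions before t1.

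A reader might also infer that the two control descriptions are incompatible and leave every between-arm effect without a defined reference. That is too strong. Study design gives a brief aside, while Control group is the dedicated section, and the therapist section's mention of supervised control-group therapists fits it. One routine consultation with optional further contacts is a coherent reading. The flaw is that neither section says so.

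Finally, the persistence shares and t2 differences above are illustrative. They show that the therapy effect is not identified; they do not predict a bias.

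**Conclusion.** The point holds as a limit on what may be concluded. As worded, one secondary hypothesis invites a conclusion about the short psychotherapy that two arms randomised once cannot support, and its timing conflicts with both sections that describe the individual sessions. The number of sessions is also inconsistent. The t2 part of the principal hypothesis should be worded for the package, because by t2 the intervention arm has been offered more than the group programme. The control condition needs a single statement.

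A reader might infer that the t2 comparison is invalid or the trial underpowered because of this. Neither follows: the package-versus-control comparisons at t1 and t2 rest on the randomisation, and N = 162 is untouched. The verdict assumes that there is no second randomisation, which is what the visible text describes.

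**What to change.** 1. Reword the secondary hypothesis as further change from t1 to t2 in the INPART package arm versus control, with no attribution to the short psychotherapy.
2. Word the t2 part of the principal hypothesis as the effect of the INPART package (group programme plus individual sessions).
3. Give one number and one timing for the individual sessions in Intervention, Main study hypotheses and Study design, and report uptake descriptively. The protocol already records treatment-process information but does not name session attendance, so a simple count per partner should be specified.
4. Define the control condition once: one structured consultation of about 30 minutes plus the booklet, with any optional further contacts part of usual care. Correct Study design to match.
5. Record and describe these contacts in both arms, but do not adjust the primary comparison for them. They arise after randomisation and belong to the comparator, so the general statement that other interventions are taken into account in the analysis should not be applied to them as an adjustment.

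The cost is protocol wording and a session count. The sponsor gives up a separate claim for the short psychotherapy. Keeping it by re-randomising at t1 would leave only 40 and 41 partners to detect it, so rewording is the better choice.
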